#### Control Group

Control group participants were neither assigned nor asked to select a target for reducing their mobile screen. They were provided with standard information regarding the advantages of reducing their mobile screen time and received reminders to do so. They will not receive any monetary incentives for reducing their mobile screen time.

All participants, including the control group, received identical information regarding the advantages of reducing mobile screen time. All participants were informed that they would receive a fixed amount of INR 500 (US $6.06) upon completing the study. Additionally, participants in the study who report their mobile screen time every week will have the opportunity to win 1 of 2 lotteries, worth INR 5000 (US $60.55) each.

### Study Procedures and Stages

The study has 5 stages: preregistration, baseline, group allocation, intervention, and postintervention, as presented in Figure 2.

**Figure 2 figure2:**
[figure not shown]
An overview of the study.

#### Preregistration

Over 2 weeks, we conducted preregistration to gather expressions of interest. A total of 327 individuals expressed interest in the study. The individuals who displayed interest in the study were requested to complete the baseline survey, which included information regarding demographics, daily mobile phone time, past attempts to reduce screen time, willingness to reduce screen time, and GAD-7 and PHQ-9 for assessing anxiety and depression (a list of collected data is summarized in Table 1). Participants were also asked to report their daily mobile screen time and upload screenshots of the digital well-being app for the week before preregistration.

The digital well-being tools offer a daily overview of a person’s phone use: the number of times the user checks their phone and the screen time. The screen time measures the total and app-wise time of the phone use. Participants share their mobile screen time through a weekly survey asking them to fill in the total time in hours and minutes of screen time for each day as displayed in the digital well-being app. As proof, the participants were asked to upload a screenshot of the digital well-being app for that week. A screenshot of the digital well-being app is shown in Figure 3. The study team checks whether the screen time in the survey matched with the screenshot. The study team provided step-by-step visual instructions for the process of uploading the screenshot from the digital well-being app. Of the 327 individuals interested in the study, 207 provided consent and completed the baseline survey.

**Table 1 table1:** Data collection at various stages of the study.

Data category	Expression of interest	Baseline^a,b^	End of intervention^a,b^	End of postintervention^a,b^
Basic information and contact details	✓	✓	✓	✓
Demographic		✓		
Information on willingness, difficulty, and magnitude in reducing mobile screentime		✓		
Information about mobile use		✓		✓
Phone addiction scale	✓	✓		✓
Generalized Anxiety Disorder–7		✓	✓	✓
Patient Health Questionnaire–9		✓	✓	✓

^a^Daily mobile screen time use: participants share their daily screen time and upload screenshots of their screen time by using the digital well-being feature on their Android mobile phones through self-administered weekly surveys.

^b^Daily mood survey: mood data are collected daily through WhatsApp messages, using a 1-10 scale that is sent at varied times of the day.

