#### Baseline (Mobile Screen Time)

The 2-week period following the preregistration was the baseline period. Every Sunday during this period, we emailed participants who had completed the baseline survey. They were instructed to provide their daily mobile screen time for the preceding week and upload a screenshot of the digital well-being app on their phones. Two reminder emails were sent to those who did not respond. Additionally, participants received a daily mood survey via WhatsApp (Meta) every day. Throughout the 2-week baseline period, 156 participants shared their mobile screen time for at least 1 week, while those who did not respond were excluded from the study.

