#### Group Allocation

The 1-week period after the baseline was the group allocation period. During this period, the 156 participants who shared their mobile screen data were randomly assigned to 1 of 3 study groups. Initially, participants in the self-selected group were given information regarding their baseline average daily mobile screen time and asked to choose a target for reducing their mobile screen time based on this average. After the participants in the self-selected group had made their specific target choices, an email was sent to participants in the assigned group informing them about their given target.

All participants, including the control groups, received an email about the benefits of reducing mobile screen time and their baseline average daily mobile screen time.

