### Statistical Analysis

We will estimate the effects of mobile screen time, target achievement rate, GAD-7, PHQ-9, and daily mood scores by comparing variables of interest between the intervention and baseline and between the postintervention and baseline periods. To perform this analysis, we will use Stata 17 and R (version 4.2.2; Free Open-Source Software). The unadjusted effects will be calculated as differences in the means and conducting a 2-tailed Student *t* test for significance. For adjusted effects, we will use simple ordinary least square regression adjusting for participant-level covariates: age, gender, and employee or student. We assume errors to be correlated within each participant but uncorrelated across participants. A separate equation will be used for each dependent variable. The regression equations are provided in Multimedia Appendix 1. For mobile screen time, we will estimate a difference-in-difference ordinary least square regression. To account for the impact of the intervention and the postintervention period, we will incorporate dummy variables for the period. Specifically, assessing the effect on mobile screen time and target achievement rate postintervention will provide valuable insights into habit formation. Multilevel or hierarchical linear modeling will also be used to allow differential relationships between mood and screen time at the individual level.

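### GAD-7 and PHQ-9 effects are worded as change from a baseline period that the only pre-treatment scores probably precede, and the score is not a listed covariate

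*Protocol article*

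**What the plan says.** **Order of the stages.** The Protocol article lists preregistration and baseline as separate stages. On the first it says "Over 2 weeks, we conducted preregistration to gather expressions of interest". The survey described there covers "willingness to reduce screen time, and GAD-7 and PHQ-9 for assessing anxiety and depression", and its completion is reported in the same section: "Of the 327 individuals interested in the study, 207 provided consent and completed the baseline survey". The section Baseline (Mobile Screen Time) then says "The 2-week period following the preregistration was the baseline period", and "Every Sunday during this period, we emailed participants who had completed the baseline survey". That section names only screen time and daily mood as data collected. Next comes allocation: "The 1-week period after the baseline was the group allocation period". No GAD-7 or PHQ-9 is mentioned there.

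**Table 1.** Each scale has one pre-treatment tick, in the Baseline column, and none under expression of interest. It is repeated at the end of the intervention and at the end of the postintervention period.

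**Analysis.** For screen time, target achievement, GAD-7, PHQ-9 and mood alike, Statistical Analysis plans on "comparing variables of interest between the intervention and baseline and between the postintervention and baseline periods". Difference-in-difference regression is named for screen time only. The covariates listed for adjusted effects are age, gender and employee or student status. The regression equations are in Multimedia Appendix 1, which is not at hand.

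**The concern.** The article uses one word, baseline, for a survey and for a 2-week period that appears to come after that survey. For screen time and mood the reference is the period. For GAD-7 and PHQ-9 it can only be the survey, yet the analysis section treats all outcomes as compared with the same baseline.

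Three things are at stake:

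- A change in GAD-7 or PHQ-9 from this survey to follow-up includes weeks in which nobody was treated. Term workload or the start of daily self-monitoring could move the scores in those weeks.
- The third objective relates change in screen time to change in mental health, and the two changes would start in different windows.
- A score already collected before randomization is not among the listed covariates. Precision is scarce here: 156 participants were randomized against a target of 300, and the Limitations section concedes that power may be too low.

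**Working it through.** **Inputs.** Preregistration 2 weeks (Preregistration); baseline 2 weeks (Baseline); allocation 1 week (Group Allocation); intervention 5 weeks (Intervention Period); postintervention 4 weeks (Postintervention Period); enrollment 21 August to 2 September 2023 and data collection ending in November 2023 (Abstract, Results).

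**The plan's own figure.** 2 + 1 + 5 + 4 = 12 weeks, which reproduces the stated duration. The 2 preregistration weeks lie outside it.

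**Reading A: survey completed during preregistration.**
- To the start of the intervention: (0 to 2) + 2 + 1 = 3 to 5 weeks.
- To the end of the intervention: add 5, giving 8 to 10 weeks.
- Untreated share: 3/8 = 38% to 5/10 = 50%.

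**Reading B: survey completed during the baseline period.**
- To the start of the intervention: (0 to 2) + 1 = 1 to 3 weeks.
- To the end of the intervention: 6 to 8 weeks.
- Untreated share: 1/6 = 17% to 3/8 = 38%.

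**Calendar check.** Assume the baseline period began on 3 September, the day after enrollment closed. The intervention then starts on 24 September, 22 days after 2 September and 34 days after 21 August (3.1 to 4.9 weeks). The postintervention period ends on 25 November, which fits the stated end of data collection. This supports the stage lengths. It does not show on which day the survey was filled in.

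**Choosing between the readings.** Preregistration reports the 207 completions within that stage, and the baseline emails went to people "we emailed participants who had completed the baseline survey". Both favour Reading A. Reading B draws on the Baseline column of Table 1 and on the Recruitment section, which mentions the survey together with screen time reporting in the baseline period. Reading A is the more natural, but the text does not settle it.

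**What the lag does to the estimate.** Let δ be the change that all arms would show from survey to follow-up without treatment, and τ the effect in an arm.
- Within one arm, expected change = δ + τ. The untreated weeks enter through δ.
- Between arms, (δ + τ₁) − (δ + τ₀) = τ₁ − τ₀. The lag cancels, because the survey precedes randomization and has the same timing in every arm.

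**Precision.** Take the variance of an unadjusted between-arm comparison of follow-up scores as 1, with equal variances at both times and correlation r between survey and follow-up. Adjusting for the survey score gives 1 − r². Comparing change scores gives 2(1 − r). The documents give no r, so the range below is an assumption:

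| r | adjusted | change score |
|---|---|---|
| 0.5 | 0.75 | 1.00 |
| 0.6 | 0.64 | 0.80 |
| 0.7 | 0.51 | 0.60 |
| 0.8 | 0.36 | 0.40 |

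The difference is 2(1 − r) − (1 − r²) = (1 − r)², which is never negative. Adjustment is therefore never worse than the change score, whatever r is.

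**Screen time nearer to the scales.** Preregistration also asked for daily screen time, with screenshots, for the week before that stage. Counting weeks from the start of preregistration, that week is centred at −0.5 and the baseline period at +3. For a survey completed at week t, the earlier week is nearer if t + 0.5 < 3 − t, that is, t < 1.25. If the article means the week before each person's own preregistration, the gap could be smaller still.

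**The case against.** The strongest reply is that this is a controlled trial. The survey was taken before allocation, on the same schedule in every arm, and reporting of screen time and mood also applied to all arms. A reader might infer that the early scores bias the randomized comparison. They do not, and that part of the reply stands in full.

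The timing is also less certain than Preregistration alone suggests. Table 1 and Recruitment allow a survey within the baseline period. The 5-week and 50% figures need a survey on the first day of preregistration, although consent came after the expression of interest. Figure 2 and the appendix might settle the date. So 3 to 5 weeks is the likelier range, not an established one.

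Nor is the mismatch with screen time complete, since a week of earlier screen time was requested alongside the survey. Asking long questionnaires once at enrollment is a defensible way to limit burden.

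A reader might also want to put a figure on the precision lost by measuring early. If a later score raised the correlation with follow-up from 0.6 to 0.7, adjusted variance would fall by 1 − 0.51/0.64 = 20%. Nothing in the documents says that a shift of a few weeks would do this, so no such saving can be claimed.

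What the reply leaves standing is the analysis wording. The appendix equations may already contain arm contrasts and the survey score. The article's own text says neither for GAD-7 and PHQ-9.

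**Conclusion.** The point holds in a limited form. On the most natural reading, the only pre-treatment GAD-7 and PHQ-9 scores precede the baseline period and lie about 3 to 5 weeks before the intervention; the other reading gives 1 to 3 weeks. The sections need reconciling either way.

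Arm comparisons are not biased. The damage is confined to three places: a period-versus-baseline change would include untreated weeks (38% to 50% of the interval to the end of the intervention on the first reading, 17% to 38% on the second); precision is forgone if the survey score is left out of the model; and the third objective would compare changes that start in different windows. The size of any drift, and of any gain in variance, is not known from the documents.

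The conclusion rests on the stated stage lengths and on the article's text without its appendix. It does not mean that the mental health results of the current cohort are invalid.

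**What to change.** **For the current cohort (wording and analysis only, no new data):**

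1. State when the survey was completed, from the survey platform's records if they show it, and bring Recruitment, Preregistration, Baseline (Mobile Screen Time) and Table 1 into line.
2. In Statistical Analysis, name that value as the pre-randomization GAD-7 or PHQ-9 score. If it was taken at preregistration, say that it precedes the baseline period.
3. Estimate GAD-7 and PHQ-9 effects as between-arm contrasts at the end of the intervention and at the end of the postintervention period, adjusted for that score together with age, gender and employee or student status. Do not report within-arm change from the baseline period as an effect.
4. For the third objective, add a sensitivity analysis that measures screen time change from the week before preregistration. It is most useful where the survey was completed early in that stage.

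All 156 participants are already randomized, so a new baseline cannot be collected for them.

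**For a repeat or extension:** include both scales again in the last weekly survey of the baseline period, closed before any group or target email goes out. Use that value as the baseline and keep the earlier one as a further covariate and as a fallback if it is missing. The cost is 7 + 9 = 16 items, once, in a survey that already goes to every participant.

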**Figure 3 figure3:**
[figure not shown]
A screenshot of the digital well-being app.

#### Baseline (Mobile Screen Time)

The 2-week period following the preregistration was the baseline period. Every Sunday during this period, we emailed participants who had completed the baseline survey. They were instructed to provide their daily mobile screen time for the preceding week and upload a screenshot of the digital well-being app on their phones. Two reminder emails were sent to those who did not respond. Additionally, participants received a daily mood survey via WhatsApp (Meta) every day. Throughout the 2-week baseline period, 156 participants shared their mobile screen time for at least 1 week, while those who did not respond were excluded from the study.

#### Group Allocation

The 1-week period after the baseline was the group allocation period. During this period, the 156 participants who shared their mobile screen data were randomly assigned to 1 of 3 study groups. Initially, participants in the self-selected group were given information regarding their baseline average daily mobile screen time and asked to choose a target for reducing their mobile screen time based on this average. After the participants in the self-selected group had made their specific target choices, an email was sent to participants in the assigned group informing them about their given target.

All participants, including the control groups, received an email about the benefits of reducing mobile screen time and their baseline average daily mobile screen time.

#### Intervention Period

The period of 5 weeks following the group allocation is the intervention period. During this, the participants will receive an email every Sunday asking them to report their mobile screen time for the preceding week and provide a screenshot. Two reminder emails will be sent to those who do not respond. Additionally, participants will continue to receive a daily mood survey through WhatsApp. Every Wednesday, we will send out reminders to all groups via WhatsApp with information about the benefits of reducing mobile screen time and details about 2 lotteries. Participants in both intervention groups will also receive email reminders for their chosen and assigned targets. Participants in the intervention groups will receive a daily incentive of INR 50 (US $0.61) for successfully meeting their daily target. These incentives will be transferred to the participants via the Unified Payments Interface after the intervention period. At the end of the intervention, an end-of-intervention survey will be administered to all participants.

#### Postintervention Period

The 4-week period following the intervention period is the postintervention period. During this, the participants will continue to receive an email requesting them to report their mobile screen time for the previous week and provide a screenshot. Two reminder emails will be sent to the participants who do not respond. Participants will also continue to receive a daily mood survey through WhatsApp. The participants will not receive monetary incentives for achieving their targets during this phase. After the postintervention period, an end-of-postintervention survey will be conducted.

### Data Collection and Management

The following data are collected during various stages of the study (Table 1). Detailed survey instruments are presented in Multimedia Appendix 1.

We collect data through a web-based survey link shared over an email. All survey instruments are created using Qualtrics (Qualtrics International Inc), a secure web-based survey and database administration application. Data privacy is maintained with password protection for access to the Qualtrics platform. Only members of the research team have access to the database. We use the user-friendly WhatsApp platform for the daily mood survey to gather mood ratings on a scale. Upon concluding the study, the mood survey data will be extracted from WhatsApp and integrated with other data for subsequent analysis.

A pilot study was conducted with the implementing department (Max Institute of Healthcare Management) employees to evaluate and refine the study procedures and the survey tools.

### Statistical Analysis

We will estimate the effects of mobile screen time, target achievement rate, GAD-7, PHQ-9, and daily mood scores by comparing variables of interest between the intervention and baseline and between the postintervention and baseline periods. To perform this analysis, we will use Stata 17 and R (version 4.2.2; Free Open-Source Software). The unadjusted effects will be calculated as differences in the means and conducting a 2-tailed Student *t* test for significance. For adjusted effects, we will use simple ordinary least square regression adjusting for participant-level covariates: age, gender, and employee or student. We assume errors to be correlated within each participant but uncorrelated across participants. A separate equation will be used for each dependent variable. The regression equations are provided in Multimedia Appendix 1. For mobile screen time, we will estimate a difference-in-difference ordinary least square regression. To account for the impact of the intervention and the postintervention period, we will incorporate dummy variables for the period. Specifically, assessing the effect on mobile screen time and target achievement rate postintervention will provide valuable insights into habit formation. Multilevel or hierarchical linear modeling will also be used to allow differential relationships between mood and screen time at the individual level.

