In addition, existing research has also shown that temporary monetary incentives and targets can be used to inculcate behavioral change in domains such as gym attendance [17], smoking, work behavior [18], alcohol abuse [19], and weight loss [20]. Research studies suggest that temporary monetary incentives and specific targets can effectively reduce social media use and allow people to limit their screen time [21].

However, the current body of research does not provide evidence regarding whether self-selected targets or externally imposed targets are more effective in promoting and maintaining behavioral change, especially in the context of smartphone use, thereby improving mental health. Reducing smartphone screen time is essential for maintaining a healthy and productive lifestyle.

In this study, we aim to nudge people to reduce their screen time by providing temporary monetary incentives and targets. Target is defined as the minimum percentage reduction in daily mobile screen time from the daily average mobile screen time during the baseline period.

The objectives of the study are as follows:

To estimate the impact of monetary incentives and targets on reducing mobile screen time during the treatment and posttreatment period.To evaluate the efficacy of self-selected versus assigned targets in reducing mobile screen time.To estimate the impact of screen time reduction on mental health. Mental health will be assessed using measures such as Generalized Anxiety Disorder–7 (GAD-7) for anxiety, Patient Health Questionnaire–9 (PHQ-9) for depression, daily mood survey for mood, and well-being scores for general well-being.

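### For GAD-7, PHQ-9 and daily mood the article states the effect only as change from baseline, so change common to all arms would count as effect

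*Protocol article*

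**What the plan says.** The Statistical Analysis section of the protocol article opens with one definition for five outcomes: mobile screen time, target achievement rate, GAD-7, PHQ-9 and daily mood. Their effects are to be estimated "by comparing variables of interest between the intervention and baseline and between the postintervention and baseline periods". It continues: "The unadjusted effects will be calculated as differences in the means", with a two-tailed Student t test. It does not say whether that test is paired, and it names no arm.

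The adjusted analysis is ordinary least squares "adjusting for participant-level covariates: age, gender, and employee or student", with a separate equation for each outcome. On the error structure it says: "We assume errors to be correlated within each participant but uncorrelated across participants". The equations themselves are elsewhere: "The regression equations are provided in Multimedia Appendix 1".

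One outcome then receives a controlled contrast: "For mobile screen time, we will estimate a difference-in-difference ordinary least square regression". No matching sentence exists for GAD-7, PHQ-9 or mood. Mood also gets a multilevel model of its relation to screen time within individuals.

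**The concern.** The trial randomises to two intervention arms and a control, so that change which would have happened anyway can be subtracted. A before/after comparison does not subtract it.

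The article itself gives reasons to expect such change. The Control Group section states: "All participants, including the control group, received identical information regarding the advantages of reducing mobile screen time". Under Group Allocation, every participant is told their own baseline average. Under Intervention Period, all groups get a weekly WhatsApp reminder about the benefits of less screen time, daily mood prompts and weekly reporting of screen time. Table 1 shows GAD-7 and PHQ-9 repeated at three time points. Calendar effects and regression to the mean can add to this.

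If scores improve in all arms, the stated definition credits the incentives and targets. If they worsen in all arms, it can hide a benefit. Either way, a mental health result reported under this definition would be an uncontrolled one inside a randomised trial.

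**Working it through.** **The plan's own figures.** The article gives no figure for the mental health comparison. Its only sizing figure, a target of 300, is for between-arm effects (d = 0.12 and 0.15). A plain two-sided comparison does not reproduce it: d = 0.12 needs 1,091 per intervention arm, or 2.5 × 1,091 ≈ 2,728 in total at 1:2:2. Nothing below uses that figure.

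**Inputs from the article**
- Randomised: 156, in a 1:2:2 ratio. Control: 156 × 1/5 ≈ 31. Intervention arms pooled: 156 × 4/5 ≈ 125. One intervention arm: about 62.
- Two-tailed test, alpha .05.

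**Assumed inputs, not in the article**
- Pre/post correlation r from .5 to .7.
- Drift shared by all arms from 0 to 0.3 SD.
- No true difference between arms.

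**Paired before/after test.** With outcome SD 1, the SD of change is √(2(1 − r)), which is 1.00 at r = .5 and 0.775 at r = .7. The noncentrality is drift ÷ (SD of change) × √n. For n = 125 and drift 0.2:
- r = .5: 0.2 ÷ 1.00 × 11.18 = 2.24, rejection 60%.
- r = .7: 0.2 ÷ 0.775 × 11.18 = 2.89, rejection 82%.

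Rejection rates with no arm effect (noncentral t; each range runs from r = .5 to r = .7):

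| Shared drift (SD) | Paired, pooled intervention (n = 125) | Paired, one arm (n = 62) |
|---|---|---|
| 0 | 5% | 5% |
| 0.1 | 20-30% | 12-17% |
| 0.2 | 60-82% | 34-52% |
| 0.3 | 91-99% | 64-85% |

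**If the t test were unpaired.** The article leaves this open. In 20,000 simulated trials at n = 125, the unpaired version rejects 0.1-0.6% of the time with no drift, 25-29% at 0.2 SD and 71-77% at 0.3 SD. It is too conservative without drift and still reacts to drift.

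**Between-arm test of change (125 vs 31).** The expected contrast is (arm effect + drift) − drift = arm effect, so shared drift cancels. In the same simulations it rejects in 4.5-5.3% of trials at every drift tried.

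**Price in precision.** The standard error of the between-arm contrast is the SD of change × √(1/31 + 1/125) = 0.201 × SD of change. For the before/after contrast it is 1/√125 = 0.089 × SD of change. The ratio is about 2.2. At 80% power (multiplier 1.96 + 0.84 = 2.80) the detectable difference between pooled intervention and control is 0.44 to 0.56 SD, against 0.19 to 0.25 SD for before/after.

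**The case against.** The strongest reply is that the deciding text is not visible. Each outcome has its own equation, the equations are in Multimedia Appendix 1, and those for GAD-7, PHQ-9 and mood may carry arm or arm-by-period terms. Elsewhere the article thinks in arms: the sample size rests on between-arm differences, the section on the assigned group explains that equal average targets allow the two groups to be compared, and the Discussion predicts which arm will do better. On this view the period-versus-baseline wording only describes the time axis of change scores that are later compared by arm.

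This stands in part. A reader might infer that the control arm is discarded for mental health altogether. The documents do not support that, because the adjusted models are unseen. What remains is that the one effect definition printed covers all five outcomes and names no arm, the unadjusted t test follows directly from it, and the article did spell out a controlled contrast where it addressed screen time.

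A second reply is that the third objective is worded "To estimate the impact of screen time reduction on mental health", which is not an arm contrast, and that the multilevel model for mood addresses it. That is true, and it means that not every mental health conclusion rests on the before/after comparison. But a before/after difference does not identify the impact of reduced screen time either, and the multilevel model covers only mood.

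A reader might also infer that the type I error is wrong in any case, or that the test is run unpaired or on daily rows. The article says none of this. A paired test with no drift holds 5%, pairing is not specified, and GAD-7 and PHQ-9 are collected once per time point, so they have no daily rows.

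**Conclusion.** The point holds for the article's effect definition and its unadjusted test. For GAD-7, PHQ-9 and daily mood only a comparison with baseline is stated, while screen time gets a contrast that removes shared change. The consequence is conditional: a paired test in about 125 intervention participants gives false-positive rates of roughly 20-30% at an assumed drift of 0.1 SD and 60-82% at 0.2 SD, with an assumed correlation of .5 to .7, and none beyond the nominal 5% without drift. The article makes shared change plausible but gives neither its size nor the correlation. Whether the adjusted models already contain the arm contrast cannot be judged from what is shown. I would class this as something that should be fixed, with medium confidence.

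**What to change.** In the Statistical Analysis section, define the effect on GAD-7, PHQ-9 and mood, separately for the intervention and postintervention periods, as the between-arm difference in change from baseline or the baseline-adjusted between-arm difference. Name both contrasts: pooled intervention versus control, and self-selected versus assigned. This matches what is stated for screen time. If the appendix equations already contain these terms, say so in the article.

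For the unadjusted test, use one value per participant per period (for mood, the participant's period mean) and compare change between arms. Report within-arm before/after change as description only.

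The cost is a few sentences of analysis text and no new data. Estimates will be less precise than a before/after contrast because the control arm has only about 31 participants; the article's Limitations section already concedes low power.
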